#### Cost-effectiveness analyses

The cost-effectiveness will be conducted from the perspectives of the hospital, health care payers, patients, and society. Analyses will be conducted for the short-term of the trial and for the lifetime of participants using modeling techniques and data from the literature, using the established cost-effectiveness analyses measures common to participating CHART projects. Effectiveness will be measured using Quality Adjusted Life Years (QALYs) which will be calculated using the EQ-5D-5L 
[26]. See Table 
2 for all measures related to cost-effectiveness. Incremental cost-effectiveness ratios (ICERs) will be calculated by dividing the net cost of Decide2Quit by its effectiveness, that is, QALYs saved by the intervention. ICERs will be calculated if Decide2Quit is effective in improving QALYs and is more expensive than usual care. Ratios will be compared to others published in the literature to determine if the Decide2Quit intervention is cost-effective. ICERs do not need to be calculated if Decide2Quit is cost-saving, that is, more effective and not more costly than usual care. To examine the robustness of and the impact of parameter uncertainty on these results, univariate and multivariate sensitivity analyses 
[42] will be used.

In addition, a non-parametric bootstrap method 
[43-46] will be used to sample with replacement costs and outcomes from usual care and intervention arms. In cost-effectiveness analyses, non-parametric bootstrapping is one of the methods used to allow the comparison of arithmetic means of cost data, which usually are heavily skewed to the right. In the case the cost data are distributed normally, we will use parametric statistical testing. The bootstrapping also is used to examine uncertainty in cost-effectiveness analyses. Relying on a conventional confidence interval of the cost-effectiveness ratio is complicated by the fact that a positive ratio indicates a case of the intervention being more effective and more costly than the comparison (and thus may be cost-effective) and indicates a case of an intervention being less effective and less costly than the comparison. A depiction of cost and effect differences of the bootstrap samples on a cost-effectiveness plane will allow us to better consider these cases and understand the variability around the ratio. The difference in costs and outcomes of each bootstrap sample, obtained by repeating the procedure 1000 times, will be plotted in a cost-effectiveness plane. An acceptability curve then will be obtained by considering the proportion of bootstrap replications for which the CE ratio falls below each possible value of cost per QALY, including the commonly used $100,000/QALY. This information will allow a better understanding of the probability of the Decide2Quit intervention being cost-effective.

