**Methods:**

A total of 1,488 patients aged 19 or older, who smoked cigarettes in the previous 30 days, are being recruited from 27 patient care areas of a large urban university hospital. Study-eligible hospitalized patients receiving usual tobacco cessation usual care are offered study referral. Trained hospital staff assist the 744 patients who are being randomized to the intervention arm with registration and orientation to the intervention website. This e-mail and web-based program offers tailored messages as well as education, self-assessment and planning aids, and social support to promote tobacco use cessation. Condition-blind study staff assess participants for tobacco use history and behaviors, tobacco use cost-related information, co-morbidities and psychosocial factors at 0, 3, 6, and 12 months. The primary outcome is self-reported 30-day tobacco abstinence at 6 months follow-up. Secondary outcomes include 7-day point prevalence quit rates at 3-, 6-, and 12-month follow-up, 30-day point prevalence quit rates at 3 and 12 months, biologically confirmed tobacco abstinence at 6-month follow-up, and multiple point-prevalence quit rates based on self-reported tobacco abstinence rates at each follow-up time period. Healthcare utilization and quality of life are assessed at baseline, and 6- and 12-month follow-up to measure program cost-effectiveness from the hospital, healthcare payer, patient, and societal perspectives.

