1	Self-efficacy for abstinence	Single question	X		X	X
3	Self-efficacy for abstinence	SEQ12	X		X	
2	Alcohol use	Audit-C	X		X	X
2	Depressive symptomology	PHQ-2	X		X	X
2	Saliva cotinine, exhaled CO, surrogate corroboration^d^	Validate 7-day smoking status			X	

^a^Tier 1 = common to all CHART trials, Tier 2 = common among some CHART sites, Tier 3 = this site only.

^b^Month 0 = Baseline.

^c^Some data collected after hospital discharge from electronic medical records and discharge summaries.

^d^Randomly selected sample of past-7-days smokers and all past-7-days non-smokers.

**Table 3 T3:** Data collection for cost effectiveness analysis

**Cost**^**a**^	**Tier**	**Data item**	**Description**	**Valuation**			
Cost of usual care	1	LHC staff time	LHC staff time spent at bedside	Average time per patient			
	1	Hospital nurse time	Time spent by assigned nurse assembling discharge packet (containing usual care)	Average time per patient			
	1	Materials	Cost of printing	Actual costs			
Cost of intervention	1	Hospital Quit Staff training	Time of trainers and trainees, materials, and so on	Study records			
	1	Hospital Quit Staff time	Time spent on each patient in preparation, implementation, and documentation of website registration/orientation and 7-14 days post-discharge follow-up call	Average time per patientWeb tracking			
	1	Quit Advisor time	Time spent on each patient in preparation, implementation, and documentation of responses to patient-generated messages	Average time per message			
	1	Patient materials	Brochures, booklets, and so on	Study records			
	1	Web site implementation (not development)	(To be determined, though may contain maintenance, servers, programming, content updating, emailing, and so on)	Study records			
	1	Time of participant on website	Time recorded on website per personal login; number, frequency, and content of messaging to Quit Advisor through the *Decide2Quit* website	Website tracking			
				Month/Source			
				0	3	6	12
Healthcare-related costs	2	Health care utilization	Hospitalizations, outpatient visits, procedures, Emergency Room visits (last 6 months) (No/Yes - # times)	X		X	X
	2	Time cost related to care	Time (hours) off work for participant and others who accompany participant to visits	X		X	X
			Gender-age group average wages for the state	Bureau of Labor Statistics			
	2	Out-of-pocket (OOP) costs	Copayments, deductibles, transportation, parking, meals, and so on (including caregivers, when applicable) (last 6 months)	X		X	X

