### Power estimate

Power is estimated for the primary outcome: differences in self-reported smoking abstinence rates between the two treatment conditions at 6 months post-hospitalization based on 30-day point prevalence. Rates for smoking cessation reported in the literature for ‘usual’ post-hospitalization care are 5% to 15% at 6 months and 7% to 10% at 1 year 
[37]. With 1,488 participants, 744 assigned to each treatment condition, using 12% as an estimated rate for the comparison group, this study will be powered (β = 80%-type II error, α = 0.05-type I error) to detect a difference of 5.12% between the two treatment conditions (two-sided). For the intervention condition, a sub-analysis between the group with one of three diagnoses (CHF, AMI, or pneumonia-expected *n* = 256) and the group with all other diagnoses (expected n = 488) will have sufficient power (β = 80%-type II error, α = 0.05-type I error) to detect a difference in tobacco abstinence rates of 9.4% (two-sided), assuming the three-diagnoses comparison group has a 25% quit rate (two-sided). Note that, as the smoking cessation rate increases for the comparison group, a larger difference is necessary between groups to achieve a specific level of power, which is why a higher rate is used for power computation. The reverse of this is true as well: as the comparison group rate decreases, a smaller difference between groups achieves the same level of power.

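### The within-trial cost-effectiveness comparison is described without adjustment for baseline EQ-5D-5L or prior utilization, so it gives up precision that data already collected could supply

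*Protocol article*

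**What the plan says.** The Abstract (Methods) gives the schedule: "Healthcare utilization and quality of life are assessed at baseline, and 6- and 12-month follow-up to measure program cost-effectiveness". Table 3 confirms that the EQ-5D-5L is taken at months 0, 6 and 12. It lists utilization at the same visits, described as "Hospitalizations, outpatient visits, procedures, Emergency Room visits (last 6 months".

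Cost-effectiveness analyses sets the measure of benefit: "Effectiveness will be measured using Quality Adjusted Life Years (QALYs) which will be calculated using the EQ-5D-5L". The ICER is net cost over QALYs gained, and it is computed only if the intervention improves QALYs and costs more. For uncertainty, a non-parametric bootstrap "will be used to sample with replacement costs and outcomes from usual care and intervention arms", repeated 1000 times. The cost and effect differences from each replicate are plotted on the plane and feed the acceptability curve. The stated purpose is to compare arithmetic means of skewed cost data. No covariate appears at any step.

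Primary and secondary outcomes analyses, a separate subsection, says that factors found unbalanced at baseline will be adjusted for in later models. The tests it names are t-tests and chi-square tests, with significance at P ≤ 0.05. The covariates listed later in that subsection concern the quit rate and include neither quality of life nor utilization.

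**The concern.** With utilities at months 0, 6 and 12, the usual area-under-curve QALY contains the baseline value itself, with weight 0.25. Baseline is also likely to be correlated with the later values. A chance difference between arms in bedside utility therefore passes into the QALY difference. Bringing the baseline value into the comparison removes that component at no data cost.

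This matters because a within-trial QALY gain from a few extra percentage points of quitters is likely to be small, and because the sign of the QALY difference decides whether an ICER is reported.

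**Working it through.** **Plan's own figure.** The Power estimate section gives: "With 1,488 participants, 744 assigned to each treatment condition, using 12% as an estimated rate for the comparison group", a detectable difference of 5.12 points, two-sided, with "β = 80%-type II error, α = 0.05-type I error" (the 80% is evidently power). A two-proportion calculation for 12% v 17.12% at 744 per arm gives 80.0% power, so the figure reproduces. The article states no figure for QALYs or costs.

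**Inputs.** From the article: n = 744 per arm; visits at 0, 6 and 12 months; 5.12 points; $100,000/QALY. Assumed, because the article does not give them: the area-under-curve formula; equal utility SD s at each visit (0.25 below; range 0.15 to 0.30); equal correlation r between visits (0 to 0.7); a utility gain per extra quitter of 0.02 to 0.10, held for a full year; complete follow-up.

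**Formulae.**
- QALY = 0.25·U0 + 0.5·U6 + 0.25·U12
- Var(QALY) = (0.375 + 0.625r)·s²
- Cov(QALY, U0) = (0.25 + 0.75r)·s², so the slope on baseline is 0.25 + 0.75r
- R² = (0.25 + 0.75r)² / (0.375 + 0.625r)
- Adjusted SE = unadjusted SE × √(1 − R²)
- SE of the baseline mean difference = s·√(2/744) = 0.25 × 0.0518 = 0.0130

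**Results at s = 0.25.**

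| r | R² | SE unadjusted | SE adjusted | Reduction in SE | QALY shift from a 1-SE baseline imbalance |
|---|---|---|---|---|---|
| 0 | 0.17 | 0.0079 | 0.0072 | 9% | 0.0032 |
| 0.3 | 0.40 | 0.0097 | 0.0075 | 23% | 0.0062 |
| 0.5 | 0.57 | 0.0107 | 0.0071 | 34% | 0.0081 |
| 0.7 | 0.74 | 0.0117 | 0.0060 | 49% | 0.0100 |

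R² and the percentage reduction do not depend on s or n. At r = 0.5 the gain equals multiplying the sample size by 1/(1 − 0.57) ≈ 2.3. A 1-SE imbalance at r = 0.5 is worth 0.0081 × $100,000 = $810 per patient. Over s = 0.15 to 0.30 and r = 0.3 to 0.7, the 1-SE shift runs from 0.0037 to 0.0121 QALY.

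**Against the likely effect.** 0.0512 × 0.02 = 0.0010; 0.0512 × 0.05 = 0.0026; 0.0512 × 0.10 = 0.0051 QALY. The shift from chance imbalance is of the same order or larger. Adjustment does not settle the sign, however. With a true gain of 0.0026, s = 0.25 and r = 0.5, the chance of a negative estimate is Φ(−0.0026/0.0107) ≈ 41% unadjusted and Φ(−0.0026/0.0071) ≈ 36% adjusted.

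**The balance-test rule.** If it did reach this analysis, a test at P ≤ 0.05 would leave imbalances of up to about 1.96 SE unadjusted. At s = 0.25 and r = 0.5 that is 1.96 × 0.0081 ≈ 0.016 QALY, or about $1,590 per patient using the unrounded shift.

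**Costs.** No cost SD or correlation with baseline utilization is given, so no gain can be calculated.

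**The case against.** The strongest reply is that this is a condensed article and covariates for the economic analysis may sit in a fuller plan that is not shown. That stands as a limit: the article nowhere declares the differences unadjusted, and the full plan may already adjust. But the section sets out the comparison from resampling by arm to the acceptability curve, and no step uses baseline data.

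Second, the article does have an adjustment rule. It belongs to another subsection and refers to later models, whereas the economic text describes no regression for the arm difference. Even if it applied, a significance test is a poor way to choose covariates: baseline utility merits adjustment because it is prognostic.

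Third, a reader might infer that the planned result is biased, or that adjustment would rescue the sign of the QALY difference. The documents support neither. Randomization makes the unadjusted difference unbiased, and the bootstrap spread already includes chance imbalance. On the assumptions above with s = 0.25, the adjusted SE remains larger than the assumed effect.

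Fourth, baseline is measured at the hospital bedside, so its correlation with later utility may be weak. That is fair, and it is why r = 0 is shown: the reduction is then 9%, because baseline is still part of the QALY.

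**Conclusion.** The point holds as a loss of precision and of accuracy conditional on the observed baseline, not as a question of validity. For the within-trial QALY difference, leaving out baseline EQ-5D-5L forgoes a reduction in standard error of about 9% to 49% as r goes from 0 to 0.7. This rests on the area-under-curve formula and on equal SDs and correlations across visits. The comparison with the likely QALY effect rests further on an assumed SD and utility gain per quitter, and shows only that chance imbalance can be as large as the effect.

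For costs the argument is directional only. The point does not extend to the lifetime analysis, which relies on modelling and literature data. The change is worth making, but the planned analysis is not wrong without it.

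**What to change.** State in the analysis plan that, regardless of any baseline test:

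- within-trial QALYs will be regressed on arm plus baseline EQ-5D-5L utility;
- within-trial costs will be regressed on arm plus baseline 6-month utilization or cost;
- both regressions will be run in each of the 1000 bootstrap replicates, keeping each participant's costs, QALYs and baseline values together, so that the plane and acceptability curve use adjusted differences.

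The unadjusted differences can be kept as a sensitivity analysis. The cost is a sentence or two of text and a small programming change; no new data are needed.

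### The acceptability curve scores bootstrap replicates by whether the cost/QALY ratio is below the threshold, so replicates in which Decide2Quit costs more and loses QALYs count as cost-effective

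*Protocol article*

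**What the plan says.** All of this is in the Protocol article, Data analyses, Cost-effectiveness analyses.

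- The ratio comes from "dividing the net cost of Decide2Quit by its effectiveness, that is, QALYs saved by the intervention".
- The trial's own ratio is conditional: "ICERs will be calculated if Decide2Quit is effective in improving QALYs and is more expensive than usual care". A result that is more effective and no more costly is treated separately as cost-saving.
- Costs and outcomes are bootstrapped, the differences being "obtained by repeating the procedure 1000 times" and plotted on a cost-effectiveness plane.
- The text sees a difficulty with confidence intervals for the ratio: "a positive ratio indicates a case of the intervention being more effective and more costly than the comparison", but it also "indicates a case of an intervention being less effective and less costly than the comparison". Its answer is that a plot on the "cost-effectiveness plane will allow us to better consider these cases and understand the variability around the ratio".
- The acceptability curve is then the "proportion of bootstrap replications for which the CE ratio falls below each possible value of cost per QALY", "including the commonly used $100,000/QALY". Plane and curve together are meant to show how probable it is that the programme is cost-effective.

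No quadrant condition and no net-benefit rule is attached to the curve.

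**The concern.** A ratio does not order results correctly once the QALY difference can be negative. Dominant replicates (cheaper, better) and dominated ones (dearer, worse) both have negative ratios, so a rule that only asks whether the ratio is below a positive threshold cannot separate the best outcome from the worst. Among replicates that are cheaper and worse, a low ratio means little is saved per QALY given up, so the inequality should be reversed.

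The text recognises that a positive ratio is ambiguous. It does not mention that a negative ratio is ambiguous too, and it then uses the ratio as the counting rule.

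Cost-effectiveness is the second of the two aims under Study design, and the Discussion ties adoption by other hospitals to the programme being both effective and cost-effective. A curve that reads high when there is no QALY gain could mislead that decision.

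**Working it through.** **Notation.** C is the cost difference and E the QALY difference, intervention minus usual care. λ is the threshold, here $100,000/QALY as named in the article. The written rule counts a replicate if C/E < λ. The net-benefit rule counts it if λE − C > 0.

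**Step 1. Single replicates (no distributional assumptions).**

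| Replicate | C | E | C/E | Written rule | λE − C | Net-benefit rule |
|---|---|---|---|---|---|---|
| Dearer, better | +300 | +0.01 | +30,000 | counted | 1,000 − 300 = +700 | counted |
| Dearer, worse | +300 | −0.01 | −30,000 | counted | −1,000 − 300 = −1,300 | not counted |
| Cheaper, better | −300 | +0.01 | −30,000 | counted | 1,000 + 300 = +1,300 | counted |
| Cheaper, worse, small saving | −300 | −0.01 | +30,000 | counted | −1,000 + 300 = −700 | not counted |
| Cheaper, worse, large saving | −2,000 | −0.01 | +200,000 | not counted | −1,000 + 2,000 = +1,000 | counted |

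The second and third rows have the same ratio and opposite meanings. The last two rows show the reversed test.

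**Step 2. General form.** Multiplying C/E < λ by E keeps the inequality when E > 0 and reverses it when E < 0. So:

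- written rule = P(E > 0 and λE − C > 0) + P(E < 0 and λE − C < 0);
- net-benefit rule = P(E > 0 and λE − C > 0) + P(E < 0 and λE − C > 0).

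For E < 0 the written rule counts exactly the replicates it should reject. As λ grows, the sign of λE − C becomes the sign of E. The written curve then tends to 100% and the correct curve to P(E > 0).

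**Step 3. Illustrative size.** The article states no expected cost or QALY difference, no variances and no probability of cost-effectiveness, so there is no figure of its own to reproduce. The assumptions are 744 per arm (the article's figure), QALY SD 0.2, cost SD $5,000 or $20,000, a true cost difference of $200, and C and E normal and independent. Standard errors are SD × √(2/744):

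- QALYs: 0.2 × 0.05185 = 0.0104;
- cost: 5,000 × 0.05185 = $259, or 20,000 × 0.05185 = $1,037.

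The net-benefit probability has a closed form, Φ[(λ × gain − 200) / √((λ × SE of E)² + (SE of C)²)]. With gain 0 and cost SD $5,000 it is Φ[−200 / √(1,037² + 259²)] = Φ(−200/1,069) = Φ(−0.187) = 0.43. The written rule was simulated with 1,000,000 draws or more.

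| True QALY gain | Cost SD | Written rule | Net-benefit rule |
|---|---|---|---|
| −0.01 | $5,000 | 95% | 13% |
| 0 | $5,000 | 90% | 43% |
| +0.005 | $20,000 | 75% | 58% |
| +0.01 | $5,000 | 93% | 77% |
| +0.02 | $5,000 | 98% | 95% |
| +0.03 | $5,000 | 99.7% | 99.6% |

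Check of the zero-gain row with the Step 2 identity: P(E > 0 and λE − C > 0) is 41.3% by simulation, and the net-benefit total is 42.6%. So P(E < 0 and λE − C > 0) = 1.3%, and P(E < 0 and λE − C < 0) = 50 − 1.3 = 48.7%. The written rule gives 41.3 + 48.7 = 90.0%. Dominated replicates are 39% of the total, and all of them are counted.

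**Step 4. Limit.** At a threshold of 10⁹ the written rule gives 100% in each of the first three rows. Net benefit gives 17%, 50% and 69%, which is P(E > 0) in each case.

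**The case against.** The best reply is that one condensed sentence in a journal article is being read as an algorithm. The article cites bootstrap methods that are not at hand, and the analysts may well use a net-benefit or quadrant rule. The surrounding text can be read that way. It limits the ICER to results that are dearer and better and treats cost-saving results separately, so a dominated result has no ICER. Carried to the replicates, with cost-saving ones counted in favour, this gives 41% against 43%, 12% against 13% and 51% against 58% in the zero-gain, −0.01 and +0.005 scenarios. That is close to the correct curve, or conservative. The plane would also show a cloud of dominated replicates beside the curve, and the stated determination of cost-effectiveness rests on comparing the ratio with published ones, not on the curve alone.

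Part of this stands. The curve is a display of uncertainty shown with the plane. The caveat in the text concerns positive ratios only. The size depends on assumed inputs and is small when the QALY gain is clear.

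It does not rescue the rule. The restriction on the ICER governs whether the trial's ratio is reported, and the article does not extend it to replicates. Applied to them literally, it would drop the dominant replicates as well. Plotting the plane does not change how the curve is counted. The article states a counting rule and states it wrongly, so this is not a detail left to a fuller document.

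**Conclusion.** The concern holds. Followed as written, the rule counts every dominated replicate in favour of Decide2Quit at every positive threshold, reverses the test among cheaper and worse replicates, and reaches 100% at high thresholds regardless of the data. That much is arithmetic and needs no assumptions.

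The size does rest on assumptions, because the article gives no cost or QALY variances. The overstatement at $100,000/QALY runs from 82 percentage points (95% against 13%) under a small harm, through 47 points (90% against 43%) at no effect, to 3 points (98% against 95%) at a gain of +0.02. The curve is thus least reliable when the QALY effect is near zero or negative, which is when it matters most. The defect is confined to the cost-effectiveness aim. The primary abstinence analysis and the sample size are untouched.

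**What to change.** Replace the counting rule with this: at each threshold, the curve is the proportion of the 1,000 bootstrap replicates with positive incremental net monetary benefit, that is, threshold × QALY difference − cost difference > 0. Report the share of replicates in each of the four quadrants beside the plane and the curve. State that the restriction on calculating ICERs applies to the trial's point estimate and not to individual replicates.

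The cost is a sentence or two in the plan and one line of code. The same bootstrap samples are used, and no new data are needed.
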